## Abstract

**Background:**

Parastomal hernias (PSHs) are common, troubling the lives of people with permanent colostomy. In previous studies, retromuscular keyhole mesh placement has been the most-used technique for PSH prevention but results have been controversial. Additionally, surgical treatment of PSHs is associated with a high rate of complications and recurrences. Therefore, it is crucial to find the most effective way to prevent PSHs in the first place without an increased risk of complications. Due to a lack of adequate research, there is no clear evidence or recommendations on which mesh or technique is best to prevent PSHs.

**Methods/design:**

The Chimney Trial is a Nordic, prospective, randomized controlled, multicenter trial designed to compare the feasibility and the potential benefits of specifically designed, intra-abdominal onlay mesh (DynaMesh®-Parastomal, FEG Textiltechnik GmbH, Aachen, Germany) against controls with permanent colostomy without mesh.

The primary outcome of the Chimney Trial is the incidence of a PSH detected by a computerized tomography (CT) scan at 12-month follow-up. Secondary outcomes are the rate of clinically detected PSHs, surgical-site infection as defined by the Centers for Disease Control and Prevention (CDC), complications as defined by the Clavien-Dindo classification, the reoperation rate, operative time, length of stay, quality of life as measured by the RAND-36 survey and colostomy impact score, and both direct and indirect costs. For each group, 102 patients were enrolled at attending hospitals and randomized at a ratio of 1:1 by browser-based software to receive a preventive mesh or a conventional colostomy without a mesh. Patients will be followed for 1 month and at 1, 3, and 5 years after the operation for long-term results and complications.

**Discussion:**

The Chimney Trial aims to provide level-I evidence on PSH prevention.

**Trial registration:**

ClinicalTrials.gov, ID: NCT03799939. Registered on 10 January 2019

## Introduction

### Background and rationale

Abdominoperineal resection (APR) with permanent end-colostomy formation was introduced in the late twentieth century as a surgical method to treat distal rectal cancer in order to decrease the previously high incidence of local recurrence [1, 2]. Despite the rising trend of saving sphincter function, APR still remains the primary operation of choice for patients with low rectal cancer [3]. Even more, the low Hartmann’s procedure with permanent colostomy is increasingly performed in older and frailer patients who are not suitable for an anastomoses [4].

The reported incidence of parastomal hernias (PSHs) with permanent end colostomy rises to 81% after long-term follow-up [5]. Due to increased use of minimally invasive rectal cancer surgery and better survival, an increased incidence of PSHs might be expected [6, 7]. Many PSHs are asymptomatic, and clinical examinations can reveal only some of them compared with computed tomography (CT) scans [7, 8]. Most PSHs are diagnosed within 2 years after the construction of the stoma, but their incidence increases after longer follow-up [5, 9, 10].

The results of PSH repair are still unsatisfactory due to a high rate of complications [11]. Therefore, the initial focus should be on prevention, which is recommended in guidelines by the European Hernia Society [11].

Several randomized control trials (RCTs) and meta-analyses have shown positive results for synthetic meshes utilized as prophylaxis with various techniques and meshes [5, 6, 12–19]. Trials have demonstrated a lower incidence of PSHs without a higher risk of complications. However, despite the use of a prophylactic mesh, the incidence of PSHs has been surprisingly high. Clinically detected hernias are present in up to 10.6–16.4% of patients with a parastomal mesh, and the incidence of radiologically detected hernias is 32.4–36.6% on recent meta-analyses [18, 20]. Additionally, a recently published RCT [21] reported similar rates of radiologically detected PSHs at 1 year after open APR in patients with (32%) and without (34%) a prophylactic retromuscular sublay mesh.

Polyvinylidene difluoride mesh (PVDF, DynaMesh®-IPST, FEG Textiltechnik GmbH, Aachen, Germany) is a synthetic mesh with a 4-cm-long, central, seamless tube (chimney) designed to repair and prevent PSHs. There are three case series [22–24] published on its use as a prophylactic mesh. In 2008, Berger et al. [22] found no clinically detectable hernias by CT scan at 1-year follow-up. In another trial, [23] the incidence of PSHs was clinically found 3.2% and in CT scans 6.4% at the 1-year follow-up in a case series of 31 patients. The prophylactic method was safe with no unexpected complications. No RCTs have been published so far. The design of the mesh with a central tube forming a stocking-like lining around the bowel may be crucial for PSH prevention [22] and blocking stomal-orifice enlargement occurring with keyhole techniques [13].

### Objectives

The objective of this study is to compare prospectively in a randomized setting the feasibility and potential benefits of specifically designed, intra-abdominal, onlay mesh (DynaMesh®-IPST, FEG Textiltechnik GmbH, Aachen, Germany) with controls having conventional colostomy without mesh in patients operated on with minimally invasive surgery.

There are very few studies on specially designed PVDF mesh in PSH prophylaxis, but the concept of tight, tube-fashioned mesh surrounding the bowel and stomal orifice might be beneficial. We hypothesize that the high rate of PSHs seen in previous trials with retromuscular keyhole mesh is due to the central hole, and the drawback may be avoidable with the use of specially designed PVDF mesh.

### Trial design

The Chimney Trial is designed as a prospective, randomized, controlled, multicenter, single-blinded study of patients who had undergone either mini-invasive laparoscopic and robotic-assisted APR or low Hartmann’s procedure for rectal adenocarcinoma. The trial is independent from any kind of industrial sponsorship.

Previous research on PVDF mesh used for PSH prevention is scarce. We conduct and evaluate the complications and adverse events of PVDF mesh for safety reasons for 30 patients who have completed 30 days’ follow-up in a group with the mesh and another group with a conventional colostomy without a mesh. If there are 10% or more serious complications defined by Clavien-Dindo classification 3B in either group, the trial will be regarded as unethical and will be terminated. For the same safety reasons, there will be further analyses on the effectiveness and complications when 30 patients in both groups have reached the 1-year follow-up. If the PSH rate is increased by more than 35% in the control group compared with the PVDF-mesh group or there are 10% or more complications defined by Clavien-Dindo classification 3B in either group compared with the other group, the trial will be terminated as unethical to continue. In case of terminating the trial prematurely, the data collected and potential complications are published.

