## Methods

### Allocation

All analyses will be performed by or under the guidance of professional statisticians and following the CONSORT guidelines [26].

Patients are randomly allocated to the study group according to a computer-generated list, compiled by a biostatistician who is not involved in the clinical care of trial patients. The randomization is performed in blocks, where the block size varies randomly between two, four, and six patients. A separate randomization list is created for each center. The software designed for the study is used to randomize the patients. After confirmation of patients’ eligibility and their willingness to participate, the randomization is completed at the outpatient visit prior to surgery and the patients are kept blinded to study technique.

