### Statistical methods

The primary endpoint will be the incidence of PSHs detected by CT scan with 95% confidence intervals for all groups at 1-year follow-up. Secondary outcomes are the incidence of PSHs at 3- and 5-year follow-ups and the development of quality of life during the follow-ups. The analyses will be based on the intention-to-treat principle. The primary endpoint and other categorical data will be analyzed by the χ^2^ test or Fisher’s exact test. Analysis of variance (ANOVA) will be used for continuous variables. For repeatedly measured data, the linear mixed model (LMM) will be used for continuous data and the generalized linear mixed model (GLMM) will be used for categorical data. Multiple imputations of missing outcome data will be used for sensitivity analyses. The SPSS statistical programs (IBM Corp. 2016. IBM SPSS Statistics for Windows, Version 24.0. Armonk, NY, USA) and SAS (version 9.4, SAS Institute Inc., Cary, NC, USA) will be used for the analyses.

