## Discussion

The aim of this study is to assess, in a randomized, multicenter setting, the safety and efficiency of specially designed, funnel-shaped PVDF mesh (DynaMesh®-IPST, FEG Textiltechnik GmbH, Aachen, Germany) in PSH prevention compared with a control group without a mesh, all being operated on using mini-invasive laparoscopic/robotic methods. The hypothesis is that the high incidence of up to 32% of PSHs detected on CT scans after retromuscular sublay mesh [21] can be reduced and further repair of PSHs can be prevented with the use of a chimney-like tube in the PVDF mesh.

Research on specially designed PVDF mesh as prophylaxis is limited but promising with a PSH incidence rate of 6.4% at 1-year-CT follow-up [23]. No RCTs using this mesh exist so far. All previous case series [22–24] included a small number of patients with no controls thus providing inadequate evidence for efficiency and safety for more routine use of this prophylactic mesh.

The focus of the current study is on the incidence of PSHs at both short- and long-term follow-up.

PSHs are not only graded by European Hernia Society Classification [25], but also the exact size and content of hernias upon the Valsalva maneuver are measured as well as the development of measurements throughout the follow-up. Radiological risk factors for PSH development will be determined as part of radiological follow-up. All symptoms caused by a stoma itself or a PSH are recorded to analyze the clinical significance of clinically or radiologically detected PSHs. The quality of life is measured by both RAND-36 and the colostomy impact score and recorded throughout the follow-up period as part of defining the clinical significance of PSHs. The re-operation rate and operations done for PSH are recorded in both groups.

This trial is designed as a single-blinded study for safety reasons. In the case of serious complications demanding re-operation, it is crucial for decision-making purposes to always have instant access to all technical aspects of the surgery. Patients are blinded to the method used during their hospital stay. Unfortunately, it is impossible to blind patients beyond that time due to direct access to the national medical database including all medical records and hospital stays.

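### The ward-laparotomy exclusion and the first safety look's completion wording can take re-laparotomies and early deaths out of the stopping rule, and they contradict the article's intention-to-treat principle

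*Protocol article*

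**What the plan says.** **First look (Trial design).** Complications and adverse events are evaluated "for 30 patients who have completed 30 days’ follow-up in a group with the mesh and another group with a conventional colostomy without a mesh". The trial ends "If there are 10% or more serious complications defined by Clavien-Dindo classification 3B in either group".

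**Second look (Trial design).** It takes place "when 30 patients in both groups have reached the 1-year follow-up". Its complication limit is "10% or more complications defined by Clavien-Dindo classification 3B in either group compared with the other group".

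**Exclusion criteria.** The list includes a complication that leads to a laparotomy while the patient is still on the ward after the operation.

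**Allocation.** Here "the randomization is completed at the outpatient visit prior to surgery".

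**Statistical methods.** "The analyses will be based on the intention-to-treat principle".

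**Outcomes and Discussion.** The secondary outcomes include re-operations and Clavien-Dindo complications of every grade, I to V, at 30 days. The Discussion says that the "re-operation rate" is recorded in both groups.

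**Data collection, management and analysis.** Complications are all recorded and monitored on a dedicated form. Data gathered before a withdrawal are still analysed.

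**The concern.** A ward laparotomy can happen only after randomisation and after the stoma, with or without mesh, has been made. It is a possible consequence of the treatment, yet the article lists it as a reason for exclusion. It is also among the events that the safety rule is meant to catch. The Discussion itself says: "In the case of serious complications demanding re-operation, it is crucial for decision-making purposes" that technical details of the surgery be at hand.

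The first look adds a second route. Its sentence describes the evaluated patients as having *completed* 30 days, and a patient who dies on day 10 has not done so.

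If both provisions are applied literally, some of the worst early outcomes fall outside the count. The limit is reached at only three events, so one or two uncounted patients can decide whether the trial continues. The reported re-operation and complication rates would be affected in the same way, and the mesh comparison too if the mesh changes the risk of early re-operation.

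**Working it through.** **1. The provisions side by side.**
- *Order of events.* Randomisation comes before surgery (Allocation) and a ward laparotomy comes after it, so this exclusion acts after randomisation. Removing such a patient conflicts with intention to treat (Statistical methods).
- *Outcome or exclusion.* The same event belongs to the re-operation outcome and to the complication outcome (Outcomes). It cannot both be counted there and remove the patient.
- *Who is in the 30.* The first look names patients who have completed 30 days. The article does not say whether a patient who died, withdrew or met the ward-laparotomy criterion belongs to the 30 or to the event count.
- *Text in favour of keeping them.* Data collection retains data up to withdrawal and records all complications. It does not mention patients who meet an exclusion criterion after surgery.

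**2. The limit in events.** I read the first look as 30 patients per group. Then 10% × 30 = 3 events. The article states no operating characteristic for this rule, so there is no figure of its own to reproduce.

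**3. What one uncounted patient does.** Suppose 3 of the first 30 operated patients in one arm have an event: 3/30 = 10.0%, and the limit is reached. If one of the three is left out and not replaced, the rate is 2/29 = 6.9%. If the next patient without an event fills the place, it is 2/30 = 6.7%. Either way the limit is missed.

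**4. Illustration of the chance of reaching the limit.** The inputs below are assumptions, because the article gives neither:
- p = true 30-day risk of an event counted by the rule (read as grade 3B or worse, including death)
- f = share of patients with such an event who are not counted; the look is taken once 30 counted patients are available

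Risk among counted patients: q = p(1 − f)/(1 − pf).

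For p = 0.10:
- f = 0.25: 0.075/0.975 = 0.077
- f = 0.50: 0.050/0.950 = 0.053
- f = 0.75: 0.025/0.925 = 0.027

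One arm: P(X ≥ 3) with X ~ Binomial(30, q). For q = 0.10 this is 1 − (0.0424 + 0.1413 + 0.2277) = 0.589.

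Either arm, same risk and same share removed in both: 1 − (1 − P)². For q = 0.10 this is 1 − 0.411² = 0.831.

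One arm reaches 3 of 30:

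| True risk | f = 0% | 25% | 50% | 75% |
|---|---|---|---|---|
| 5% | 0.188 | 0.104 | 0.041 | 0.007 |
| 10% | 0.589 | 0.409 | 0.208 | 0.047 |
| 15% | 0.849 | 0.698 | 0.443 | 0.132 |
| 20% | 0.956 | 0.874 | 0.663 | 0.258 |

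Either arm reaches 3 of 30:

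| True risk | f = 0% | 25% | 50% | 75% |
|---|---|---|---|---|
| 5% | 0.340 | 0.197 | 0.080 | 0.014 |
| 10% | 0.831 | 0.651 | 0.373 | 0.091 |
| 15% | 0.977 | 0.909 | 0.690 | 0.246 |
| 20% | 0.998 | 0.984 | 0.886 | 0.449 |

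The first look stops on either group, so the second table matches the rule. The first table shows its sensitivity when only one arm is at raised risk. Neither applies directly to the second look, whose limit is worded as a comparison between groups.

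**The case against.** The strongest reply is that nobody is in fact lost. Completion of 30 days may only fix when the look is taken. Complications of all grades are recorded, data before withdrawal are kept, and analysis is by intention to treat. Loss to follow-up needs three consecutive missed visits, while Table 1 schedules only one visit after discharge up to day 30. Before the first look, then, only death, withdrawal of consent or the exclusion itself could remove a patient. The exact safety set is also something that a condensed article may leave to the full protocol.

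Much of this stands, and it rules out several stronger readings that a reader might infer:
- *That the looks count completers only and replace everyone else.* The article contains no replacement rule, and the timing reading is open.
- *That both looks depend on completion.* Only the first uses that wording. The second speaks of patients who have *reached* 1 year and is affected mainly through the ward-laparotomy exclusion.
- *That most serious events would vanish.* The exclusion covers laparotomy on the ward. Events treated without laparotomy, or arising after discharge, stay countable in a patient who completes 30 days.
- *That the tables estimate the actual loss.* A removal share of 0% is consistent with the Data collection and Statistical methods sections, and the larger shares have no source in the article.

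The reply does not dispose of the exclusion criterion. Recording an event on a form does not place the patient in the look, and the provision on withdrawal says nothing about patients excluded for a post-operative event. This is a conflict between statements that the article makes, not a detail left to another document.

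**Conclusion.** The point holds as a contradiction with a possible, unquantified effect. The ward-laparotomy exclusion conflicts with randomisation before surgery, with intention to treat, and with the re-operation and complication outcomes. Combined with the first look's wording, it leaves open whether ward re-laparotomies and early deaths count towards a limit of 3 in 30.

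If they do count, nothing is lost. If a quarter of event patients did not, the chance that the first look reaches its limit at a true risk of 10% would fall from 0.83 to 0.65 for either arm, and from 0.59 to 0.41 for one arm. At a half it would be 0.37 and 0.21. These figures rest on assumed risks and removal shares, on 30 patients per group, on reading 3B as 3B or worse, and, for either arm, on equal risk and equal removal in both groups. The effect on the difference between mesh and control was not calculated.

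**What to change.** Reconcile the Exclusion criteria with the Trial design, Outcomes, Allocation, Data collection and Statistical methods sections:

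1. Define each look on the first 30 randomised and operated patients per group whose scheduled day-30 or 1-year date has passed, whether or not they attended.
2. Count every event from surgery onward, including in patients who die, withdraw or meet an exclusion after the operation. For withdrawn patients, this means events up to withdrawal.
3. State that a ward laparotomy is recorded as a complication and a re-operation and does not remove the patient from the looks or from the analyses.

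The stopping limits are not touched. The cost is a wording amendment, since the complication form already collects the data. The downside is that observed complication rates may look slightly less favourable.

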### Sample size

To calculate a sample size needed to compare the two groups, we estimated a 6.4% rate of PSH and 34% PSH on a CT scan for the PVDF-mesh group and control group during 12 months’ follow-up [21, 23]. Assuming α = 0.05 and power = 90%, we would need 51 patients per group. Furthermore, assuming a 5-year drop-out rate of 50%, 102 patients per group are needed to reach statistically significant results also during long-term follow-up.

All analyses will be performed by, or under the guidance of, professional statisticians and following the Consolidated Standards of Reporting Trials (CONSORT) guidelines [26].

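### The 30-day safety rule ends the trial on an absolute 10% limit in either arm, so no-mesh control events alone can stop it; the 1-year rule has another form, and the grades that count are unclear

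*Protocol article*

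**What the plan says.** The Trial design section of the protocol article sets two safety looks.

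- **30-day look.** The sample is "30 patients who have completed 30 days’ follow-up in a group with the mesh and another group with a conventional colostomy without a mesh". The limit is "10% or more serious complications defined by Clavien-Dindo classification 3B in either group, the trial will be regarded as unethical", and the stated consequence is that "the trial will be regarded as unethical and will be terminated". No comparison between arms and no review step is given.
- **1-year look.** It takes place "when 30 patients in both groups have reached the 1-year follow-up". The complication limit is now "10% or more complications defined by Clavien-Dindo classification 3B in either group compared with the other group", again with termination. A separate limit on the hernia rate applies at this look and is not at issue here.

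Three other places bear on the rule. The secondary outcomes list Clavien-Dindo grades I to V at 30 days. The exclusion criteria remove patients whose postoperative complications on the ward require laparotomy. The Discussion presents the limits as clearly fixed in advance, because evidence on this mesh is scarce.

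**The concern.** The safety analysis is there to evaluate the mesh. At 30 days, however, the limit applies to each arm by itself. Three grade 3B complications among 30 controls say nothing against the mesh, and with none in the mesh arm they would favour it. The trial would still have to end.

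The 30-day look covers 60 of the 204 planned patients (2 × 30 of 2 × 102), before any of these patients' 12-month CT results could inform the decision. A stop caused by the background risk of rectal cancer surgery could cost the trial its primary question without any sign of mesh harm.

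The same 10% is an absolute level at one look and a comparison at the other. Because only grade 3B is named, two people applying the rule to the same data could also disagree on whether a grade IV or V event counts.

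**Working it through.** **The plan's own figure.** There is none to reproduce: the article states no false-stop or detection probability for the safety rule. The Sample size section gives rates for hernia only ("we estimated a 6.4% rate of PSH and 34% PSH on a CT scan for the PVDF-mesh group and control group") and no complication rate. The background 3B rate p is therefore an assumption, shown over a range.

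**Inputs.** n = 30 per arm (Trial design; the 1-year wording refers to both groups). Limit 10%, so 0.10 × 30 = 3 patients. Same true rate p in both arms, meaning no mesh harm. Arms independent; patients counted rather than events.

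**30-day look.** Let T be the chance that one arm reaches the limit:

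T = P(X ≥ 3) = 1 − [P(0) + P(1) + P(2)], with X ~ Binomial(30, p)

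Either arm stops: 1 − (1 − T)². Control arm stops while mesh does not: T(1 − T).

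At p = 0.05: P(0) = 0.2146, P(1) = 0.3389, P(2) = 0.2586, sum 0.8122, so T = 0.188. Either arm: 1 − 0.8122² = 0.340. Control alone: 0.188 × 0.812 = 0.153.

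| Assumed 3B rate, both arms | One arm (T) | Either arm: trial stops | Control arm alone |
|---|---|---|---|
| 1% | 0.003 | 0.007 | 0.003 |
| 2% | 0.022 | 0.043 | 0.021 |
| 3% | 0.060 | 0.117 | 0.056 |
| 5% | 0.188 | 0.340 | 0.153 |
| 8% | 0.435 | 0.680 | 0.246 |
| 10% | 0.589 | 0.831 | 0.242 |

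If 30 meant the total, with 15 per arm and a limit of 2, the either-arm figures are 0.141 at 3%, 0.313 at 5% and 0.565 at 8%. The picture is the same.

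**1-year look.** The result depends on how the comparison is read. X is the mesh count and Y the control count.

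- *Absolute difference of 10 percentage points, either direction:* P(|X − Y| ≥ 3) = 0.058 at 3%, 0.131 at 5%, 0.226 at 8%, 0.275 at 10%. Half of each comes from an excess in controls.
- *Relative difference of 10%:* with counts this small almost any inequality qualifies (1 against 2, or 3 against 4). At 5%, P(X ≠ Y) = 1 − (0.2146² + 0.3389² + 0.2586² + 0.1270² + 0.0451² + …) = 1 − 0.246 = 0.754.

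The two readings differ almost sixfold at the same rate.

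**What the control-arm trigger contributes.** Suppose the control rate is 5% and the mesh rate is truly raised. The chance of stopping at the 30-day look is:

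| Mesh rate | Rule as written (either arm) | Mesh arm's limit only | Mesh exceeds control by 3 or more |
|---|---|---|---|
| 5% (no harm) | 0.340 | 0.188 | 0.065 |
| 10% | 0.666 | 0.589 | 0.302 |
| 15% | 0.877 | 0.849 | 0.580 |
| 20% | 0.964 | 0.956 | 0.789 |

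Column two is 1 − (1 − T_mesh)(1 − T_control); at 20% it is 1 − (0.0442 × 0.8122) = 0.964. Column four sums the product of the two binomial probabilities over X − Y ≥ 3. The last two columns illustrate the trade-off and are not recommended limits.

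**The case against.** **The background rate is unknown and may be low.** This stands. At 1% or 2% the false-stop chance is 0.7% or 4.3%. Eligibility also points downward: open or converted surgery, ASA 4–5, emergency cases and T4b multi-organ resections are excluded. So are patients with ward complications needing laparotomy, some of whom would otherwise be graded 3B. The article does not say whether those last patients count at the look. A reader might infer that a trial with a harmless mesh is likely to be stopped; the document does not support that without a rate.

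**Caution is reasonable for a little-studied device.** This stands in part. Early stopping on a strict limit is the sponsor's choice to make, and it costs information rather than biasing the primary comparison. But caution about the mesh justifies sensitivity to events in the mesh arm. It does not explain ending the trial on control-arm events, which add under one percentage point to detection at 20% against 5% (0.964 against 0.956).

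**Grade 3B surely means 3B or higher.** This is the most plausible intention, and all complications are recorded and monitored in any case. A reader might infer that deaths and life-threatening events are deliberately left out of the rule. The text supports only that it is unclear. Counting grades IV and V would raise the stopping probabilities above those shown.

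**The 1-year rule may be read in more than one way.** Agreed. The 13% at a 5% rate belongs to the absolute-difference reading alone.

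**Conclusion.** The point holds as a defect in how the rule is fixed. Three parts rest on the text alone: the 30-day limit is absolute and lets the control arm alone end the trial; the 1-year limit has a different and ambiguous form; and the grades that count are not settled.

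The size is conditional on a rate the article does not give. With equal rates, the 30-day false-stop probability runs from about 4% at 2% to 83% at 10%. The most telling value needs no outside source: at half the protocol's own limit, a harmless mesh is stopped about one time in three, and in 15% of trials by the control arm alone. These figures assume 30 patients per arm, independent arms and one count per patient. Counting events instead of patients would make stopping likelier; leaving out patients excluded for laparotomy could make it less likely.

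This should be corrected before the 30-day look. It does not invalidate the primary comparison.

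**What to change.** Amend the Trial design section as follows.

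1. Give both looks one stated form, directed at excess harm in the mesh arm, and say whether any percentage is an absolute or a relative difference.
2. Make an absolute count in a single arm, including control, a trigger for review rather than automatic termination.
3. State the expected 3B rate in this population, and the resulting probabilities of a false stop and of detecting a harmful mesh.
4. Reconcile the 3B wording with the grades I to V collected, for example by saying whether 3B means 3B or higher. Say whether patients or events are counted, and whether patients excluded for laparotomy are included.

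The sponsor should choose the numerical threshold; none is proposed here.

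The cost is amendment wording and a short calculation, plus some sensitivity of automatic stopping. Removing only the control-arm trigger costs little: at a control rate of 5%, detection of a 20% mesh rate goes from 0.964 to 0.956, while the false-stop chance falls from 0.340 to 0.188. A fully comparative rule costs more: with 30 per arm, the illustrative difference of 3 cuts false stops to 0.065 but detection to 0.789. The review trigger on the absolute count is kept to offset that loss.

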As current results from the use of the most evaluated keyhole technique in PSH prevention are unsatisfactory, more trials are needed to define the efficiency and safety of other methods to prevent PSH. As previous research on the PVDF mesh used in this trial is limited, there are clearly predefined safety limits of PSH incidence and complications to determine when to prematurely finish the trial as unethical to continue. For the same reason, the trial is designed to compare the mesh group to control group without any mesh to detect the objective efficiency and safety of funnel-shaped PVDF mesh. Since there is a lack of long-term results of PSH prevention, the sample size is estimated to reach statistically significant results at the long-term follow-up at 5 years.

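### The 1-year efficacy stopping rule does not say whether its 35% is relative or in percentage points; read literally as relative, it stops about 21% of no-effect trials and 99% at the planned rates

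*Protocol article*

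**What the plan says.** The Trial design section of the protocol article plans "further analyses on the effectiveness and complications when 30 patients in both groups have reached the 1-year follow-up". The efficacy part of that look reads "If the PSH rate is increased by more than 35% in the control group compared with the PVDF-mesh group", and the consequence is that "the trial will be terminated as unethical to continue". No scale is given for the 35%, and no test or confidence limit goes with it. The Discussion nevertheless presents these limits as clear and fixed in advance.

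The design that the rule sits in comes from the Sample size section: "we estimated a 6.4% rate of PSH and 34% PSH on a CT scan for the PVDF-mesh group and control group". It continues "Assuming α = 0.05 and power = 90%, we would need 51 patients per group", and then "assuming a 5-year drop-out rate of 50%, 102 patients per group are needed". The Discussion adds that "the sample size is estimated to reach statistically significant results at the long-term follow-up at 5 years".

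**The concern.** An increase of 35% in a rate, taken literally, is relative: the control rate is more than 1.35 times the mesh rate. With 30 patients per group and a modest event rate, a ratio of 1.35 is well within chance. The planned rates also lie far beyond it, because 34/6.4 − 1 = 4.31, a 431% increase. On this reading a binding rule could end the trial on noise if the mesh does nothing, and would almost surely end it early if the mesh works as planned.

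Read as percentage points, the same sentence asks for more than the planned difference of 34 − 6.4 = 27.6 points.

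Whoever applies the rule may have to choose the scale with the counts in view. Ten hernias against two stops the trial on the relative reading (10 > 1.35 × 2 = 2.7) and lets it continue on the other (8/30 = 26.7 points).

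**Working it through.** **Inputs.** From Trial design: 30 per group, threshold more than 35%. From Sample size: control 34%, mesh 6.4%, α = 0.05 (taken as two-sided), power 90%, 51 per group, 102 after 50% drop-out. From Background and rationale: a trial of a different mesh technique with 32% (mesh) against 34% (no mesh) at 1 year, which makes a null near those rates realistic. Assumption not in the document: a common rate of 20%, close to the mean of the two planned rates, (34 + 6.4)/2 = 20.2%.

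**Step 1: the plan's own sample size.** With mean rate 0.202 and difference 0.276,

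n = [1.960·√(2·0.202·0.798) + 1.282·√(0.34·0.66 + 0.064·0.936)]² / 0.276² ≈ 42.4, so 43 per group.

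The continuity correction, (n/4)·[1 + √(1 + 4/(n·0.276))]², gives 50. The stated 51 is within one of this, and 51/(1 − 0.5) = 102. The design figures reproduce, so the planned rates are a fair basis for testing the rule.

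**Step 2: the two rules in counts.** Let C and M be the hernias among 30 controls and 30 mesh patients, independent binomials.

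- Relative: stop if C > 1.35·M (and C > 0).
- Percentage points: stop if (C − M)/30 > 0.35. Since 0.35 × 30 = 10.5, this means C − M ≥ 11.

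P(stop) is the sum of P(C = c)·P(M = m) over all pairs that meet the rule. The last column applies a two-sided Fisher test at p < 0.001 in favour of mesh, for comparison.

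| True rates, control vs mesh | Relative | Percentage points | Fisher p < 0.001 |
|---|---|---|---|
| 34% vs 34% | 20.6% | 0.19% | 0.02% |
| 32% vs 32% | 21.6% | 0.17% | 0.02% |
| 20% vs 20% (assumed) | 28.0% | 0.03% | 0.01% |
| 34% vs 32% | 26.1% | 0.30% | 0.04% |
| 34% vs 6.4% (planned) | 99.0% | 22.2% | 16.9% |

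The relative column counts a result with no mesh hernias and at least one control hernia as a crossing. If at least one mesh hernia were required, the 34% null figure would stay at 20.6% and the planned-rate figure would fall to 85.3%.

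**Step 3: what evidence a crossing carries.** On the relative reading, 2 vs 1 (Fisher p = 1.0), 7 vs 5 (p = 0.75) and 11 vs 8 (p = 0.58) all stop the trial. At a 34% null, about 94% of the stops have p > 0.05. On the percentage-point reading, the crossing with the smallest counts, 11 vs 0, has p = 0.0003, and the weakest of all, such as 21 vs 10, has p = 0.009.

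**Step 4: where recruitment would stand.** The look needs 60 patients with 1 year of follow-up. Assume even accrual of 204 over about 35 months (Trial status gives February 2019 to the end of 2021), or 5.8 a month. The 60th patient enters at about month 10 and the look falls at about month 22, with about 130 randomised. Over 24 months (the lower end in Recruitment), or 8.5 a month, the look falls at about month 19, with about 160 randomised. At 50% drop-out, 130 to 160 patients leave 65 × 0.5 ≈ 32 to 80 × 0.5 = 40 per group at 5 years, against the 51 planned.

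**The case against.** The strongest reply is that the authors meant percentage points. Clinical writers often say a rate is increased by so many percent when they mean points, and the neighbouring 10% complication limits are on the percentage scale. On that reading the rule is a sound early-stopping boundary. It almost never fires under the null, and every crossing carries Fisher p < 0.01. Asking for more than the expected difference is normal at an early look. This stands, but the document does not settle the scale, and the literal wording points the other way.

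A reader might infer that the rule fails under either reading, because 35 points exceeds the whole assumed control rate. The document does not support that. The 34% is an assumed true rate, not a ceiling on what is observed in 30 patients. The points rule stops 22% of trials at the planned rates, 45% if the true mesh rate were zero, and 80% if the control rate were 50% (an assumption) against 6.4%. Nor can 22% be called too seldom when a p < 0.001 boundary stops 17%.

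A reader might also infer that the trial would end with its first 60 patients. Those are the patients who trigger the look. On the accrual figures above, some 130 to 160 would already be randomised, and the protocol does not say that their follow-up would cease.

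Finally, the protocol does not say that stopping declares efficacy, so 21% is not a type I error. How the look relates to the final 5% test may be set out in an analysis plan that is not shown, and its absence here is not counted.

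**Conclusion.** The point holds as a defect of a binding rule whose scale is undefined. Under the trial's own planning rates the two readings give stopping probabilities of 99% and 22%. With no effect at a 34% rate they give 21% and 0.2%. Only the relative reading does harm: it can end the trial on differences with no evidential weight, and at the planned effect it would very probably stop recruitment short of 204 patients and weaken the 5-year comparison. The percentage-point reading is acceptable, though it does not match the planned 27.6-point difference.

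The results rest on independent binomial counts with exactly 30 evaluable patients per group. The 28% null figure also rests on the assumed common rate of 20%.

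**What to change.** Amend the efficacy paragraph of Trial design to:

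1. State the scale and exclude the relative reading.
2. Tie the stop to the between-arm test of CT-detected PSH at 1 year, with a stringent boundary. One option is Haybittle-Peto: stop for benefit only if two-sided p < 0.001 in favour of mesh with 30 per group. That gives about 0.02% false stops at a 34% null and 17% stops at the planned rates, and leaves the final test essentially at 0.05. An explicit 35-percentage-point margin performs similarly and would also be acceptable.
3. State that patients already randomised stay in 3- and 5-year follow-up if recruitment stops.

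The cost is a one-paragraph amendment and a lower chance of stopping early for benefit than under the relative reading. The sample size does not change.
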